#### Parasternal electromyography

Exacerbations of COPD result in an increase in the subjective work of breathing, anxiety and tachypnoea, which in turn result in a progressive increase in the elevated neural respiratory drive mediated through the respiratory centre in the brainstem [79–81]. Although the output of the respiratory centre cannot be measured directly, a well validated surrogate measure is the electromyography (EMG) signal measured at the level of the parasternal intercostal muscles using surface electrodes placed over the second intercostal space [80, 82–84]. Parasternal EMG has been demonstrated to be a reproducible and well tolerated technique to assess neural respiratory drive [85], particularly for patients with an exacerbation of COPD [80, 81]. To allow physiologically meaningful comparisons of the EMG signal, the root mean square is used to quantify the intensity and duration of the contraction and has been shown to be linearly associated with increasing load on the muscle [86, 87]. Additional measures to quantify the neural respiratory drive are the percentage of the EMG signal of the maximum EMG signal obtained (EMG_para%max_) and the neural respiratory drive index (NRDI), which is the product of EMG_para%max_ and the respiratory rate [80]. NRDI is a validated measure of work of breathing during an acute exacerbation and allows changes in work of breathing over time to be documented [80, 81].

EMG will be recorded from the parasternal second intercostal space bilaterally and then processed and analysed in accordance with previously published work [80, 81]. The root mean square will be used to calculate the root mean square EMG_para%max_ from the maximum EMG signal obtained and the NRDI will be calculated by multiplying EMG_para%max_ by the respiratory rate. Changes in an individual patient will then be analysed over time.

#### Oesophageal pressure monitoring

Oesophageal pressure (P_ES_) may be measured using an inflated balloon placed in the lower oesophagus and attached to an air-filled pressure transducer. The changes in P_ES_ with respiration are concordant with the changes in pleural pressure (P_PL_) [88–90]. The difference between P_ES_ and airway pressure (P_AW_) is a reasonable estimate of transpulmonary pressure (P_L_) in the region surrounding the balloon [89–91]. From this, the work of breathing can be calculated using the integration of the difference between the static compliance of the chest wall and the oesophageal pressure multiplied by volume over time. As chest wall compliance cannot be directly measured in spontaneously breathing patients, it will be estimated as normal, at 200 mL/cmH_2_O [88, 91]. Respiratory muscle work will also be estimated using the pressure time product of the oesophageal pressure (PTP_ES_) [88, 91]. PTP_ES_ is the integral of pressure over time and is the product of the change in pressure multiplied by the duration of the contraction [88, 91]. The particular advantage of PTP_ES_ is that it provides an estimate of activity regardless of whether or not a volume is generated. Due to the development of dynamic hyperinflation in exacerbations of COPD, the muscles of respiration commence contracting prior to airflow commencing [89, 92]. PTP_ES_ estimates of the work undertaken during this isometric phase of contraction. Application of extrinsic PEEP can be titrated to minimise work of breathing [91].

Oesophageal pressure measurements will be undertaken using a 5 French latex free balloon catheter (Cooper Surgical, Conneticut, USA) inserted into the lower oesophagus trans-nasally with 0.5–1.5 mL of air instilled to allow optimal transmission of the pressure waveform [91]. The catheter is attached to a pressure transducer to obtain pressure measurements and simultaneous pneumotachograph recordings are made (Hans Rudolph differential pneumotachograph). The balloon position will be validated using the dynamic occlusion test in the spontaneously breathing patient [92, 93].). All signals will be collected on a personal computer through a 12-bit analogue-to-digital converter (National Instrument DAQCard 700; Austin, TX) at a sampling frequency of 200 Hz (ICU-lab, KleisTEK Engineering, Bari, Italy). Signals will be analysed using ICU-Lab software. The oesophageal pressure trace will be used to calculate work of breathing and the pressure time product will be calculated. Oesophageal pressure will be used solely as an outcome measure and will not be available for use at the bedside.

## Safety reporting

The safety reporting window for this trial is from enrolment until completion of the interventional component of the trial (cessation of the device). Safety reporting will follow the standard operating procedure for Guy’s and St Thomas’ NHS Foundation Trust. Anticipated adverse events will be recorded as part of the trial information safety endpoints. All serious adverse events will be reported to the sponsors and manufacturer within one working day.

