## Methods/design

### Design

The trial is a prospective, randomised, controlled, with 1:1 allocation ratio unblinded study of ECCO_2_R in adults with AECOPD at risk of failing NIV as demonstrated by a persisting pH < 7.30 due to hypercapnoea after initial medical therapy and at least 1 h of NIV. The study will randomise a total of 24 patients, 12 in each treatment arm. Allocation was generated by computer-generated random number and concealed via opaque sealed envelopes.

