### Secondary outcome

Secondary outcomes include the impact of ECCO2R on:Safety, including:Incidence of haemorrhagic complications—significant haemorrhage is defined as bleeding requiring transfusion of more than one unit of blood, intracerebral bleeding, bleeding requiring procedural interventionIncidence of thrombosis—all patients will have screening duplex ultrasound of the cannulated vesselIncidence of haemolysis defined by rising lactate dehydrogenase, bilirubin red cell fragments on a blood film and/or a rising plasma free-haemoglobin (> 0.5 g/dL)Complications relating to cannulation including those at insertion—bleeding, vascular damage, pneumothorax and line infection, both clinically apparent (erythema/cellulitis at insertion site) and microbiologically proven (positive blood culture with concomitant line tip culture or line insertion site culture)Physiology, including respiratory rate, heart rate, blood pressure, temperature, arterial blood gases measured at time (T)0 min, T30 minutes, T 60 min, then every fourth hour for the first 24 h and then every sixth hour until discontinuation of the acute phase of the trialDaily spirometry including forced vital capacity, forced expiratory volume in 1 s and the ratio between themWork of breathing, including electrical impedance tomography, parasternal electromyography and oesophageal pressure (these are described in detail below)Patient outcomes:Mortality (ICU, hospital and 3 month)Length of stay (ICU, hospital)Need for intubation and where this occurs, duration of mechanical ventilation and need for tracheostomy, NIV failure and need for intubation will be decided by the clinical team managing the patient. Reason for NIV failure will be recorded by the research team.3-Month hospital readmission rateTolerance, assessed using both a numerical rating scale (0–10) and visual acuity scale (0–10 cm) for both dyspnoea and comfort with the lowest reading being extremely uncomfortable and the highest being extremely comfortable. Comparisons between the two different measures will be used without an absolute definition of comfort/discomfort.At 3-months following randomisation: COPD assessment test, St George’s Respiratory Questionnaire, EuroQoL 5D. Comparisons between the different measures will be used without an absolute definition of success at follow-up.Cost-effectiveness with ICU bed day and consumables cost/quality adjusted life year (QALY)

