### Treatment of trial participants

Following presentation, initial medical therapy and NIV will be commenced as per current local and UK national guidelines for the management of AECOPD [47]. All patients with AECOPD and pH < 7.30 after a minimum of 1 h NIV will be eligible for inclusion unless exclusion criteria are met. Once informed written consent is obtained from either the patient or their consultee if consent from the patient is not possible, patients will be randomised to the continuation of NIV alone or addition of ECCO_2_R to NIV. All other aspects of care, including acute, on-going and post-trial care, will be at the discretion of the clinical team. Monitoring will be the standard of care of ICU, including arterial and central venous access where this is deemed appropriate by the clinical team.

Patients who are randomised to continuation of NIV alone will be managed in accordance with hospital protocols and national guidelines for NIV. NIV will be titrated to achieve an arterial pH > 7.35, respiratory rate < 25 and patient comfort with breathing. Discontinuation of NIV will occur when judged appropriate by the patient’s clinician. Cessation of NIV will be defined as occurring after six continuous hours without NIV.

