#### ECCO_2_R

Patients who are randomised to addition of ECCO_2_R will undergo cannulation in either the right internal jugular vein or one of the femoral veins using a 15.5 French double lumen ECCO_2_R cannula (patient and operator preference) using an ultrasound-guided Seldinger technique. The ECCO_2_R device, will be primed with 0.9% saline and 1 unit/mL heparin in accordance with the manufacturer’s instructions. The blood flow will be titrated to the maximum achievable (usually 400–500 mL/minute) and sweep gas titrated up to 10 L/minute in 1 L/minute increments every 15 min. ECCO_2_R will be titrated to achieve an arterial pH > 7.35, respiratory rate < 25 and patient comfort with breathing. Discontinuation of NIV and ECCO_2_R will occur when judged appropriate by the patient’s clinician. Cessation of ECCO_2_R will be defined as occurring after six continuous hours without ECCO_2_R. All patients receiving ECCO2R will receive a continuous infusion of heparin to maintain an APTTr of 1.5–2 titrated using the hospital protocol. Data relating to the ICU inpatient stay will be collected from the ICU and hospital information systems. At 3 months following randomisation, a telephone interview will be conducted by the randomising study centre to ascertain the post-discharge survey data.

Whilst the patient remains on respiratory support (either NIV or ECCO_2_R), all patients will undergo daily assessment of dyspnoea and comfort, spirometry, electrical impedance tomography, parasternal electromyography and oesophageal pressure monitoring.

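### The safety reporting window ends when the ECCO2R device stops, so control patients have no defined end and later serious adverse events in the ECCO2R arm fall outside it

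*Protocol article*

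**What the plan says.** The Safety reporting section gives a single window: "The safety reporting window for this trial is from enrolment until completion of the interventional component of the trial (cessation of the device"). Serious adverse events go to the sponsor and manufacturer within one working day. On expected events it adds: "Anticipated adverse events will be recorded as part of the trial information safety endpoints".

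The ECCO2R section shows which device is meant ("The ECCO_2_R device, will be primed with 0.9% saline and 1 unit/mL heparin") and when it counts as stopped: "Cessation of ECCO_2_R will be defined as occurring after six continuous hours without ECCO_2_R".

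Only one arm receives it. Under Treatment of trial participants, "patients will be randomised to the continuation of NIV alone or addition of ECCO_2_R to NIV". Under Design, "The study will randomise a total of 24 patients, 12 in each treatment arm".

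The safety endpoints are in the Secondary outcome section. They cover significant haemorrhage, thrombosis found by duplex scan of the cannulated vessel, haemolysis, and "Complications relating to cannulation including those at insertion". The last group includes line infection, shown either by clinical signs at the insertion site or microbiologically ("positive blood culture with concomitant line tip culture or line insertion site culture"). None of these endpoints has a time limit. Mortality and readmission are followed to 3 months.

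**The concern.** A safety window should cover the same period in both arms and should not depend on the treatment received. This one closes on an event that can occur in only one arm. Two things follow.

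- Controls have no defined period over which safety events are reportable, so events that both arms can have, such as haemorrhage, have no common time base.
- In the ECCO2R arm the window closes soon after the device stops, while some of the harms listed as endpoints can appear or be confirmed later.

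The Discussion names safety data among the key aims, and the trial has no data monitoring committee. Reporting serious events to the sponsor and manufacturer is therefore the main safety oversight route that the article describes.

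**Working it through.** The plan gives no figure on this point, so the check sets the texts side by side.

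**1. End of the window, by arm.**

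| | ECCO2R arm (12) | Control arm (12) |
|---|---|---|
| Treatment | ECCO2R added to NIV | NIV alone |
| Stated end of window | six continuous hours off ECCO2R | device cessation, which cannot occur |
| Other end given | none | none |

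By the text, 12 of 24 patients (12/24 = 50%) have no defined end. The same gap applies to any patient allocated to ECCO2R who is never connected.

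**2. Can the text be read so that controls do have an end?** The interventional component could be taken to mean NIV for controls, although the parenthesis ties it to the device. Two versions of that reading are possible.

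- *End of NIV in controls, end of device in the ECCO2R arm.* The two windows would close on different events. The article gives no expected ECCO2R duration, so the difference cannot be calculated.
- *End of NIV in both arms.* The Sample size section expects mean NIV durations of 48 h and 36 h. The windows would then differ by 48 − 36 = 12 h on average if the treatment works as planned. Their length would be the primary outcome itself, with stopping left to the clinician in an open-label trial.

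Both versions give reporting periods that depend on treatment or outcome.

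**3. Listed harms against the end of the window in the ECCO2R arm.**

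- *Cannulation complications.* The wording includes those at insertion, so it is not confined to them. Later events count as endpoints.
- *Thrombosis.* It is screened by duplex of the cannulated vessel, with no timing given. The scan may fall before or after the window closes.
- *Line infection.* One of the two supporting cultures is of the line tip, which requires the line to be out. The other is of the insertion site, and clinical signs also count. Neither of these needs removal.
- *Haemorrhage.* No time limit is given.

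A serious event of any of these kinds that arises after six continuous hours off ECCO2R is therefore within the endpoint list but outside the reporting window. The two sections do not fit together.

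**The case against.** The strongest reply is that a reporting window is not the same as outcome ascertainment. The Safety reporting section handles anticipated events separately, by recording them as endpoints, and the endpoint list has no cut-off. This stands. A reader might infer that late cannula harms go uncounted, but the documents do not show that. They show only that such events are outside the stated reporting window.

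Other parts of the reply also stand.

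- The six-hour rule carries the window past switch-off, so bleeding at prompt decannulation, or a line tip sent then, could fall inside it.
- Line infection can be established without a tip culture, so this endpoint does not as a whole depend on removing the line.
- A reader might infer that screened patients will be compared with unscreened controls for thrombosis. No such test is stated. The Statistical analysis section extends the primary analysis to secondary efficacy data, and the duplex scan can only sensibly apply to cannulated patients.
- The imprecision that comes from having 12 patients in the ECCO2R arm is the same under any window, so it does not measure the effect of this one.
- Mortality, intubation, length of stay and readmission are collected regardless of the window, and the primary outcome is unaffected.

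Finally, the full protocol or the sponsor's operating procedure may add detail. That would excuse something left out, but the article states the end of the window explicitly, and the stated rule does not work for one of the two arms. The reply does not supply an end for controls, nor a stated route for a serious event that arises after the device has stopped.

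**Conclusion.** The point holds as a badly fixed rule and should be fixed. The end of the safety reporting window is undefined for the 12 control patients. The readings that would supply an end make the period depend on arm or outcome. In the ECCO2R arm, serious adverse events arising after six continuous hours off the device are outside the stated window, including kinds the trial lists as safety endpoints.

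The conclusion rests on reading the device as the ECCO2R device, which the ECCO2R section supports. The number of events affected cannot be estimated from the documents, because they give no event rates, device duration, decannulation time or scan time. The consequence shown is for reportability and for a common safety period across arms. Loss of endpoint data is not shown.

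**What to change.** Reconcile the Safety reporting and Secondary outcome sections in one amendment.

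- Define one safety window for both arms, starting at randomisation, independent of the device and extending past decannulation. A fixed day or hospital discharge would serve. A fixed day sets the same planned period in both arms, whereas discharge varies with length of stay, which is itself a secondary outcome.
- Apply that window to serious adverse event reporting and to the listed safety endpoints.
- Report cannula-specific events, including thrombosis found by duplex screening, as incidence in the ECCO2R arm.

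The cost is a short amendment and modest extra adverse-event recording in 24 patients who are already followed in hospital and to 3 months.

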## Sample size

It is estimated that the effect of addition of ECCO_2_R will be a reduction in NIV duration from 48 h to 36 h. Group sample sizes of 24 (12 in each arm) patients achieve 80% power to reject the null hypothesis of equal means when the population mean difference is 12 h with a common standard deviation of 10 h with alpha level of 5%.

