## Background

Chronic obstructive pulmonary disease (COPD) is a syndrome characterised by progressive and not fully reversible expiratory airway flow limitation. The underlying pathophysiology of COPD is the progressive destruction of the elastic and alveolar tissue within the lung, resulting in reduced expiratory flow rates, maldistributed ventilation, gas trapping and hyperinflation, which in turn lead to diaphragmatic flattening and inefficient respiration. COPD is punctuated by recurrent exacerbations characterised by a worsening of the patient’s dyspnoea, cough and/or sputum production beyond day-to-day variations [1]. Acute exacerbations are an important cause of hospital admission and impact on patients’ quality of life [2–5], as well as having a huge societal impact amounting to ~ 6% of the total healthcare cost [6]. Exacerbations also accelerate disease progression, leading to a progressive stepwise functional decline [7–13].

Patients with significant exacerbations of COPD resulting in hypercapnic respiratory acidosis (PaCO_2_ > 6 kPa (45 mmHg) and pH < 7.35) have life-threatening respiratory failure and non-invasive ventilation (NIV) has significant mortality benefits for patients [1, 14–19]. NIV provides both inspiratory and expiratory pressure, which, by splinting open collapsing airways by matching intrinsic positive end expiratory pressure (PEEP) and providing positive pressure to assist tiring respiratory muscles, enhances ventilation. This enables an improved ventilation–perfusion relationship, improves gas exchange and simultaneously reduces oxygen consumption and carbon dioxide production because of the reduction in work of the respiratory muscles [16, 20]. Although NIV has substantially improved mortality (risk ratio 0.54, 95% CI 0.38 to 0.76) and decreased the need for intubation (risk ratio 0.36; 95% CI 0.28 to 0.46) in patients with an acute exacerbation of COPD [16], 15–30% of patients commencing NIV fail and require intubation and mechanical ventilation [21–23]. Risk factors for NIV failure include obtundation, hypercapnoea, persisting respiratory acidosis (pH < 7.30), higher APACHE II score (> 28), tachypnoea (> 29) and lack of improvement in the first 1–2 h of therapy [23–27]. Patients who fail NIV and require intubation have a significantly higher mortality than those who improve with NIV (30% vs < 10%) [28], with mortality rates up to 57% in some case series [29].

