## Statistical analysis

Summary measures for the baseline characteristics of each group will be presented as mean and standard deviation for continuous (approximate) normally distributed variables, medians and interquartile ranges for non-normally distributed variables, and frequencies and percentages for categorical variables. The planned primary efficacy analyses, difference between the two arms in reduction in NIV duration, will be analysed on randomized patients using a non-parametric approach, Mann-Whitney U test. Similar analyses as for the primary outcome measure will be conducted for secondary efficacy data. Missing data in the efficacy population will not be interpolated. All randomised participants in both arms with valid non-invasive ventilation data will be included in the analysis. Analysis of the physiological data will be per protocol, whilst analysis of outcomes will be intention to treat. Physiological data will be compared within individuals to describe a relative change in work of breathing. The statistical analysis plan can be accessed through the corresponding author. No subgroups have been planned.

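### The stated 80% power is that of a t-test on 24 complete patients; the planned Mann-Whitney test has about 77% on the same normal inputs, with no reserve for NIV failure or unusable data

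*Protocol article*

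**What the plan says.** The Sample size section of the protocol article assumes "a reduction in NIV duration from 48 h to 36 h" and "a common standard deviation of 10 h". It states that 24 patients, 12 per arm, "achieve 80% power to reject the null hypothesis of equal means when the population mean difference is 12 h with a common standard deviation" as just given; alpha is 5%. It does not say whether the test is one- or two-sided, and it makes no allowance for patients who cannot be evaluated.

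The Statistical analysis section says that the primary comparison of NIV duration "will be analysed on randomized patients using a non-parametric approach, Mann-Whitney U test". The analysis takes in randomised patients with valid NIV data, missing values are not filled in, and outcomes are analysed by intention to treat.

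The Background reports that 15–30% "of patients commencing NIV fail and require intubation and mechanical ventilation", and it lists persisting acidosis with pH below 7.30 among the risk factors for failure. The Design and Inclusion criteria sections use that same pH threshold, after at least 1 h of NIV, to select patients. The Primary outcome section counts a discontinuation as successful only if the patient is free of mechanical ventilation. The article does not say what time or rank a patient who fails NIV receives.

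**The concern.** The power statement and the analysis statement describe different procedures. The first tests equality of means on 24 complete observations. The second is a rank test on however many patients have valid data. A reader of the results will set the primary p-value against the stated 80%, and that figure was not derived for the test that produces the p-value.

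The number of patients also sits exactly at the threshold, so any loss takes power below 80%. Intubation after failed NIV is the foreseeable source of loss or distortion here. An intubated patient does not fit a model of normal durations around 48 h and 36 h, whichever way the case is handled. The Discussion limits expectations for mortality and for intubation because the trial is small, but it gives no such caution for the primary endpoint.

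**Working it through.** **Inputs from the article.** Means 48 h and 36 h, so the difference is 12 h; common SD 10 h; 12 per arm; alpha 5% (Sample size). Mann-Whitney U test (Statistical analysis). NIV failure 15–30% (Background), which is a cited background rate and not a planning input.

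**1. Reproduce the stated figure.** Standardised difference d = 12/10 = 1.2. Noncentrality = d × √(n/2) = 1.2 × √6 = 2.939. Degrees of freedom = 24 − 2 = 22; two-sided 5% critical value 2.074. Power from the noncentral t distribution = **80.2%**. Variants that do not match the stated figure:

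| Calculation | Power |
|---|---|
| Normal approximation, 12 per arm | 83.6% |
| One-sided t-test, 12 per arm | 88.5% |
| Two-sided t-test, 24 per arm | 98.3% |

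Of the calculations tried, only the two-sided t-test with all 24 evaluable gives 80%.

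**2. Reserve in that calculation.** The same formula gives 76.3% at 11 per arm and 71.8% at 10 per arm.

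**3. Power of the planned test, complete data.** Simulated two-sided Mann-Whitney test, 12 per arm, means 48 and 36 h, SD 10 h in each arm:

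| Data model and version of the test | Power |
|---|---|
| Normal, exact test (or approximation with continuity correction) | about 76.5% |
| Normal, approximation without continuity correction | 78.4% |
| Lognormal with the same means and SD, exact test | 79.9% |

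With normal data and 13 per arm, the exact test gives 79.9%.

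**4. Sensitivity to NIV failure.** Three things are assumed here: the background rate applies to this trial, failure is independent of the duration the patient would otherwise have had, and it is equally common in both arms. Durations are normal as above, 12 randomised per arm.

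| Handling of failures | 15% in both arms | 30% in both arms |
|---|---|---|
| Excluded | 67–68% | 56% |
| Ranked worst | about 44% | about 23% |

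**5. Unequal failure, failures ranked worst.** Rates are NIV alone versus NIV plus ECCO2R:

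| Failure rates | Power |
|---|---|
| 15% vs 0% | 86% |
| 30% vs 0% | 93% |
| 30% vs 5% | 84% |
| 15% vs 5% | 73% |
| 30% vs 10% | 72% |
| 30% vs 15% | 58% |

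Power passes 80% only where ECCO2R removes nearly all failures. The Sample size section does not rely on such an effect.

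**The case against.** The strongest reply is that the quoted sentence contains no error. It names its null hypothesis, equal means, and its figure reproduces. That stands: this is a mismatch between the power statement and the analysis, not a miscalculation.

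The reply continues that sizing on means and analysing by ranks is common, and that the price is small. This also stands. The change of test costs between nothing and about 3.5 points, or roughly one patient per arm. Durations are positive and often skewed to the right, and under a lognormal model the 80% holds.

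A reader might infer more: that the trial's real power is 56–68%, or even 23–44%, because the article gives its own failure rate. The article does not support that. The 15–30% refers to patients starting NIV in general. This trial selects patients at higher risk but excludes those who already have an indication for intubation, so its own rate is unknown. Equal failure in both arms is a further assumption, since the Background mentions avoidance of intubation as a suggested benefit of ECCO2R. Exclusion of failures is not stated either: under intention to treat, an intubated patient may well have valid NIV data. How failures are scored may be settled in the analysis plan, which is not shown.

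What remains is that the Sample size section allows for no failures and no unusable data under any handling, while the analysis section provides for incomplete data and the eligibility criteria select for failure.

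**Conclusion.** The point holds in a limited form. The 80% is right for a two-sided t-test with complete data, but it is not the power of the stated primary analysis. For the Mann-Whitney test on the stated inputs, power is about 77% with normal durations and about 80% with lognormal ones, provided that all 24 patients are evaluable.

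The absence of any reserve matters more than the choice of test. How much power would be lost cannot be fixed from the article, because it depends on a failure rate, a balance between arms and a scoring rule that the article does not give. The figures for 15% and 30% failure illustrate sensitivity and are not estimates of this trial's power. A flat statement that the trial cannot reach 80% would also go too far, given the scenarios in which ECCO2R nearly abolishes failure and failures are ranked worst. The correction should be made, because a null primary result would otherwise be judged against a figure that belongs to another test and to complete data.

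**What to change.** In the Sample size section:

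- State that the 80% refers to a two-sided two-sample t-test with all 24 patients evaluable.
- Give the power of the Mann-Whitney test beside it: about 77% under the stated normal model with complete data.
- Add one line each for 15% and 30% NIV failure, computed under the failure handling that the analysis plan adopts. Label the rates, and the assumption about their balance between arms, as assumptions.

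This is a change of wording and a short calculation. It needs no further patients and leaves the primary analysis as it is. The cost is a less favourable stated figure.
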